**Methods/design:**

During a two-year period we recruit 300 men aged from 35 to 45 years with elevated cardiovascular risk (> two traditional risk factors). The men are randomized into three arms: 1) a health promotion intervention alone, 2) both health promotion and exercise intervention, or 3) control with usual community care and delayed health promotion (these men receive the intervention after one year). The main outcome measures will be the existence of metabolic syndrome and physical activity frequency (times per week). The participants are assessed at baseline, and at 3, 6, and 12 months. The follow-up of the study will last 12 months.

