## Methods/design

### Study design

The study is a three-arm one-center randomized controlled trial (Figure 
1). Two methods of health promotion are studied in middle-aged men with elevated cardiovascular risk. After screening and randomization, one study group receives a 1½-hour health promotion intervention by a public health nurse. The other intervention group receives, in addition to public health nurse intervention, a guided group exercise intervention of 12 weeks. The third group is randomized to serve as a control and men in this group may participate in the intervention after one year, should they wish to.

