### Outcome measures

The outcomes are measured after 3, 6 and 12 months of the randomization. The blood tests are taken at months 0, 3 and 12. Other outcomes are measured by Internet surveys and, if the participant does not respond, by telephone surveys.

Primary outcome measures will be 1) metabolic syndrome defined by International Diabetes Federation/American Heart Association
[11], thus fulfilling three or more of the following criteria:

- systolic blood pressure ≥ 130 or diastolic blood pressure ≥ 85 or specific medication;

- triglyserides ≥1.7 mmol/L or specific medication;

- HDL cholesterol < 1.0 mmol/L or specific medication

- fasting plasma glucose ≥ 5.6 mmol/L or specific medication;

- waist circumference >94 cm

2) and self-reported physical activity measured by how many times per week a participant performs vigorous exercise activity. Table 
1 shows also the secondary outcome measures.

**Table 1 T1:** Outcome measures

**Variable**	**T0**	**T1**	**T2**	**T3**
1. Primary outcome measures				
1.1 Metabolic syndrome1 (yes/no)	x	x	x	x
● Blood pressure, waist circumference,				
● Blood LDL- and HDL-cholesterol, triglycerides, blood glucose				
1.2 Physical activity	x	x	x	x
● Self-reported physical activity, exercise times, per week				
2. Other outcome measures				
● 2 km walking test (s)	x	x		x
● Self-reported general health (0–100)	x	x	x	x
● Self-reported overall stress (0–100)	x	x	x	x
● Utilisation and costs of medical services	x	x	x	x
● Individual cardiovascular risk factors: total cholesterol (mmol/L), LDL-cholesterol (mmol/L), HDL-cholesterol (mmol/L), smoking (yes/no), blood glucose (mmol/L), hs-CRP (mmol/L)	x	x	x	x
	x	x		x
● Body composition (InBody): muscle mass (kg), body fat mass (kg)	x	x		x

1 Defined by International Diabetes Federation/American Heart Association
[11].

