### Sample size

Sample sizes were calculated by statistical power analysis. We hypothesised that the percentage of men continuing the increased exercise level after one year would be 30% in the control group and 50% in the exercise group. To detect this difference with α = .05 and β = .80, 91 men in each group are needed.

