### Statistical analysis

A primary intention-to-treat analysis will be carried out. The main analyses involve standard two-sample comparisons (parametric or non-parametric depending on the distribution of the data) looking at effect sizes at 3 and 12 months.

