The results of this study assess the effects of the interventions on physical activity and cardiovascular risk. We chose physical activity as a main outcome because from earlier literature we know that if men continue on their increased physical activity level, they will gain health benefits. The cardiovascular risk is a surrogate endpoint. It would, however, not be feasible to study morbidity because onset of cardiovascular risk will take years or decades in these men. In addition to these quantitative outcomes, assessing the participants’ views on barriers and facilitators to lifestyle changes after their experiences in the trial in the qualitative analysis will be of importance.

This study will provide information on the effects of an exercise intervention on cardiovascular risk and physical activity in middle-aged men. This pragmatic trial will shed light on the success of a physical activity intervention in real life, which is a recognized challenge in studies aiming at metabolic disease control
[14]. The results of this study can be used in the planning of interventions aimed at reducing cardiovascular risk, diseases and mortality in primary care.

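### Two unranked primary outcomes are tested at two main time points in a three-arm trial, and the analysis section does not carry forward the one-year contrast on which the trial was sized

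*Protocol article*

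**What the plan says.** Study design: "The study is a three-arm one-center randomized controlled trial". The arms are a nurse-led health promotion session alone, the same session plus 12 weeks of group exercise (the combined arm), and control.

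Outcome measures lists two primary outcomes, with no order of priority and no rule on whether one or both must succeed. The first is metabolic syndrome (yes/no). The second is "self-reported physical activity measured by how many times per week a participant performs vigorous exercise activity".

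Sample size hypothesises that the percentage of men keeping up their increased exercise at one year "would be 30% in the control group and 50% in the exercise group", and concludes: "To detect this difference with α = .05 and β = .80, 91 men in each group are needed".

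Statistical analysis: "The main analyses involve standard two-sample comparisons", with the addition "looking at effect sizes at 3 and 12 months". It names no pair of arms, no leading outcome and no leading time point.

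The closing paragraph of the Discussion says: "This study will provide information on the effects of an exercise intervention on cardiovascular risk and physical activity in middle-aged men".

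**The concern.** Two outcomes, two time points and at least one pair of arms all have main status, so a favourable result on any of several tests could be presented as the trial's main finding. That matters more here because the trial is open and one primary outcome is self-reported. The Sample size section had already chosen a contrast and a time, but the analysis section uses neither to set priority.

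A second issue concerns interpretation. The exercise arm also receives the nurse session, so its difference from control is the effect of a package. The comparison that isolates exercise is combined arm against health promotion alone. No difference is planned for it.

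**Working it through.** **1. The plan's own figure.** Inputs from Sample size: 30% v 50%, α = .05 (two-sided assumed), power .80 (the article labels this β; it only makes sense as power).

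n = [p₁(1−p₁) + p₂(1−p₂)] × (z₀.₉₇₅ + z₀.₈₀)² / (p₂−p₁)² = (0.21 + 0.25) × (1.960 + 0.842)² / 0.20² = 90.3, so 91 per group. This matches. The pooled-variance formula gives 93, within 3%. The size is right for one test of one contrast at one time.

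**2. Counting the main tests.** Two outcomes × two times = 4 per pair of arms.
- Combined arm v control only: 1 × 4 = 4
- Both active arms v control: 2 × 4 = 8
- All three pairs: 3 × 4 = 12

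The article does not say which of these applies, so all three are carried.

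**3. Chance of at least one false positive, each test at .05.** If the k tests were independent, it would be 1 − 0.95^k: 18.5% (k = 4), 33.7% (k = 8), 46.0% (k = 12). The tests are not independent, because pairwise comparisons share arms and the outcomes and visits are measured on the same men. A simulation under no effect anywhere (400,000 replicates, three equal arms, normal test statistics) allows for this. The correlations are assumptions: 0 to .8 between time points and 0 to .4 between outcomes. Equal allocation is also assumed.

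| Tests | Independent | Simulated range | At time .5, outcome .2 |
|---|---|---|---|
| 4 | 18.5% | 14-19% | 17% |
| 8 | 33.7% | 25-32% | 29% |
| 12 | 46.0% | 32-41% | 38% |

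**4. Dropping 3 months alone.** With only 12 months kept and outcome correlation .2, the rates are 9.6% (one pair, 2 tests), 17% (both active arms v control, 4 tests) and 23% (all pairs, 6 tests). Naming one time point helps, but an order or another adjustment is still needed.

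**5. Splitting alpha instead.** At .025 per outcome, 30% v 50% needs 113 per group (pooled formula). Power is 70% at 91 per group and 75% at 100 (300 men in three equal arms).

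**6. The comparison that isolates exercise.** Take 50% in the combined arm, as planned, and an assumed rate p for health promotion alone, with 91 per arm and two-sided .05.

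Power = Φ[(d − 1.96 × SE₀)/SE₁], where d = 0.50 − p, SE₀ = √(2p̄(1−p̄)/91) with p̄ the mean of the two rates, and SE₁ = √([p(1−p) + 0.25]/91).

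For p = 40%: SE₀ = 0.0738, SE₁ = 0.0734, (0.10 − 0.1446)/0.0734 = −0.61, power 27%. For p = 35% it is 53%, and for p = 45% it is 10%.

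**The case against.** The strongest defence is that this is a two-sentence section of a condensed article. Adjustment rules, test order and the list of contrasts commonly sit in a statistical analysis plan, which is not shown. That stands as far as it goes: the absence of a multiplicity rule is not in itself the finding. What remains is what the article does fix, namely two main time points for two unranked primaries, set beside a size calculation for one contrast at one year. Blood is taken at 0, 3 and 12 months, which explains why 3 and 12 were chosen but does not rank them.

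Four stronger readings are tempting and go too far.
- **That the plan tests everything at .05.** Alpha appears only in Sample size; the analysis section gives no significance level and speaks of effect sizes.
- **That there is no primary contrast anywhere.** Sample size does single one out; it is just not carried forward.
- **That the error rate reaches about 45%.** That is the independence figure for 12 tests. Shared arms alone cap it at 41%, and no passage says that all three pairs will be tested.
- **That the trial will report a package effect as an exercise effect.** The article describes the combined arm openly, comparing a package with usual care is legitimate in a pragmatic trial, and the Discussion sentence is a general closing statement, not an analysis rule.

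**Conclusion.** The concern holds in a limited form. Followed as written, the main analyses carry a false-positive chance well above the only alpha stated: 14-19%, 25-32% or 32-41%, depending on whether one, two or all three pairs of arms are tested. These figures assume .05 per test, equal arms and the correlation ranges above. Even the narrowest reading is about three times the nominal 5%.

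The added effect of exercise can be estimated, but the trial was not sized for it. The power figures of 53%, 27% and 10% rest on assumed rates of 35%, 40% and 45% for health promotion alone, which the article does not give.

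The planned 80% power belongs to the percentage continuing their increased exercise. It does not transfer to the primary outcome as defined, which is a weekly frequency.

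**What to change.** - State that 12 months is the only primary time point, in line with Sample size, and that 3 months is secondary.
- Test in a prespecified order at two-sided .05, stopping confirmatory claims at the first non-significant step. For example: (1) combined arm v control on physical activity; (2) combined arm v control on metabolic syndrome; (3) health promotion v control on physical activity; (4) health promotion v control on metabolic syndrome. Which outcome leads is the sponsor's choice, provided it is fixed before outcome data are seen.
- Report combined arm v health promotion alone with its confidence interval as the estimate of the added effect of exercise, and describe combined arm v control as the effect of the package.
- Say that the planned power refers to the percentage continuing increased exercise, not to times per week.

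This changes wording only and needs no more men. The order holds the overall error at 5% or less and keeps full alpha for the first test, whereas splitting alpha would lower power as shown in step 5. The cost is that 3-month results, and any test after a failed step, can be reported but not claimed as confirmatory.

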### Qualitative analysis

In addition to quantitative methods, focus group discussions are conducted in order to study the experiences of the men in the intervention, the acceptability of the intervention and the barriers and facilitators for lifestyle change in men. The focus group discussions are held after the execution of the intervention. Using a qualitative approach we also study what the men’s experiences of the group exercise intervention are and whether they continue these activities after the trial. Also, the men’s preferred methods for joining projects aiming at lifestyle changes and other societal aspects are examined.

## Discussion

In this study, we assess the effects of primary care interventions aiming to reduce cardiovascular risk in early middle-aged men. Health promotion by public health nurses has become a popular method in cardiovascular prevention. Its effectiveness has, however, recently been questioned
[4]. At the onset of this the trial, it was clear that it had to be included it in the intervention. We also wanted to study an exercise intervention, as many cardiovascular risk factors can be controlled through exercise
[12,13].

We chose a group-based intervention because we considered the social support in the group to be an important motivational factor for the success of the intervention. Kirkkonummi is a suburban municipality, where most of the families move from other parts of Finland to work in the capital region. Many men do not have the social networks of their youth for maintaining their exercise activities. One possible result of this trial is that men continue to exercise in their intervention groups. We will follow-up for the potential societal effects of the trial using qualitative methods.

The strengths of this study are that it is a primary care pragmatic trial and that the results are readily generalizable to similar primary care settings. Also, the interventions included are feasible and non-expensive. If they prove effective, they can easily be transferred to other similar circumstances.

The study has some limitations as well. Blinding is not feasible and this study is performed as an open trial. Randomized controlled trials are not common in primary care health centers and there are threats to validity, e.g. how to guarantee similar processes by all study nurses and how to avoid other protocol violations. A special challenge is to keep the participants in the control group. As the participating men are not patients but working-aged and busy, their participation in the outcome measurements is a challenge.

The results of this study assess the effects of the interventions on physical activity and cardiovascular risk. We chose physical activity as a main outcome because from earlier literature we know that if men continue on their increased physical activity level, they will gain health benefits. The cardiovascular risk is a surrogate endpoint. It would, however, not be feasible to study morbidity because onset of cardiovascular risk will take years or decades in these men. In addition to these quantitative outcomes, assessing the participants’ views on barriers and facilitators to lifestyle changes after their experiences in the trial in the qualitative analysis will be of importance.

This study will provide information on the effects of an exercise intervention on cardiovascular risk and physical activity in middle-aged men. This pragmatic trial will shed light on the success of a physical activity intervention in real life, which is a recognized challenge in studies aiming at metabolic disease control
[14]. The results of this study can be used in the planning of interventions aimed at reducing cardiovascular risk, diseases and mortality in primary care.
